*Crossover Effects on Internalizing Symptoms and Suicide Ideation.* Although eHealth Familias Unidas does not directly address internalizing symptoms, Familias Unidas has had crossover effects on both internalizing symptoms (consisting of depression and anxiety symptoms) and suicide ideation. One study led by [name] and colleagues found that, relative to control, Familias Unidas reduced internalizing symptoms among 242 delinquent 13- to 17-year-old youth. Improvements in family communication mediated the intervention's effects on internalizing symptoms for youth whose families had poor communication. A second study of 721 Hispanic youth (14.0 years; SD=1.14) found reductions in internalizing symptoms for youth with low family communication through intervention-mediated improvements in communication across three pooled Familias Unidas trials. A third study among youth with externalizing behaviors documented cascading effects on internalizing symptoms through the intervention's impact on improving family communication, followed by subsequent reductions in externalizing behaviors, and ultimately reduced internalizing symptoms. In terms of suicide, a fourth study of a single trial showed that at baseline 9.2% of adolescents had recent suicide thoughts and 5.7% a suicide attempt, with 12.2% reporting thoughts and 8.6% reporting attempts among the 18.8% of those reporting poor family communication. This study found that Familias Unidas significantly reduced suicide attempts compared to control (OR = .53,  $p < .05$ ) for youth reporting poor family communication.

It is important to note that the effects sizes between eHealth Familias Unidas and Control vs Face-to-Face Familias Unidas and Control in prior studies have not been significantly different across the various outcomes (except for smoking which is not an outcome in this study). Additionally, participants in eHealth Familias Unidas had greater attendance than those in the face-to-face version of the intervention, and attendance in the intervention is related to improved study outcomes.

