#### 4) **Inclusion and Exclusion Criteria\***

Families will be screened based on the following inclusion criteria:

- (a) Female and male adolescents, who self-identify as Hispanic (or Latino(a))

- (b) Adolescent between the ages of 12 – 16 years
- (c) Adolescent living with an adult primary caregiver who is willing to participate
- (d) Families must have broadband internet access on a device, including (but not limited to) a smartphone, iPad, tablet, computer at their home or other location (e.g., school, library, etc.)
- (e) Families screening positive on poor family communication (a score of less than 75 on the communication measure; see measures) or youth reporting elevated depressive or anxiety symptom scores or a history of suicide behavior (ideation or attempts)

Exclusion criteria: Families reporting plans to move out of the South Florida area during the study period.

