## 5) Procedures Involved\*

**Design.** To evaluate eHealth Familias Unidas Mental Health in an effectiveness-implementation hybrid Type 1 trial, this study will use a rollout design, which is an extension of a Stepped Wedge design. We will balance, and then randomize all 18 sites into five cohorts of 4 or 3 clinics to when they would end their control phase, when they would begin receiving eHealth Familias Unidas Mental Health, and when they would start the sustainability period where UM staff would no longer provide formal support (i.e., clinical supervision) to the clinic to deliver eHealth Familias Unidas Mental Health. This design is an extension of a Stepped Wedge design since it has three conditions (as shown in the figure) and provides both within and between clinic comparisons of effectiveness over time. Youth and parents will be assessed at baseline, 3-, 6-, and 18-months post-baseline. We will collect electronic health record data (e.g., exposure to an antidepressant) for participants during their control phase.

**Participants.** The sample will consist of 468 Hispanic female and male adolescents and their primary caregivers recruited from one of 18 primary care clinics, who meet the inclusion/exclusion criteria below. We will include a mix of naive and previously involved clinics in the proposed study. Because we did not attempt to institutionalize eHealth Familias Unidas in earlier involved clinics, we do not anticipate much difference in effect, but we will test for this.

A document to assess for the inclusion/exclusion criteria will be included as part of the patient check-in process. We will screen parents and adolescents separately to verify the inclusion and exclusion criteria. Adolescents will be asked questions regarding their mental health (reporting elevated depressive or anxiety symptom scores or a history of suicide behavior) and parents will be asked questions related to communication with their adolescent.

**Recruitment.** Participants will be recruited from 18 primary care clinics.

[figure not shown]

The sites are heterogeneous and consist of federally qualified health centers, academic primary care clinics located within the University of Miami's Health District, and private community clinics. Collectively, these sites jointly serve over 10,000 Hispanic between the ages of 12 -16 per year. Therefore, we do not anticipate any challenges in recruiting 468 youth over the 18-month recruitment period.

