For continuous measures of depressive and anxious symptoms and drug misuse, we will analyze impact using growth modeling with four time points modeled as a multivariate normal distribution. For suicide behavior (i.e., ideation and attempt), and drug misuse, we will conduct generalized growth modeling with mixed effects using these repeated binary measures. For both continuous and binary outcomes, our analytical procedures will follow those we have used previously to analyze Familias Unidas trial data. For our standard analyses we will use *Mplus* to examine changes in growth using its two-level modeling of clinic and individual, commonly called three-level modeling in the mixed effect modeling literature (individuals with repeated measures nested within clinics,). Since youth are recruited from all 18 clinics both during Control and eHealth Familias Unidas Mental Health, we can consider clinic to be a “blocking

factor,” so the overall effect is essentially a mean of the differences in response across all 18 clinics. After suitable transformation of the time axis, handling of missing data, and model fit checking (see Clinical Trials Section 4B for additional details), we will use a Wald type test on the difference in mean slope parameters for eHealth Familias Unidas versus Control assigned participants. Base rates for suicide attempts are low and thus we accounted for them in our analytic plan and power analyses (see below). In a universal trial of Familias Unidas, found that at baseline 9.2% of youth reported suicide ideation and 5.7% reported a suicide attempt in the preceding year. We have presented power analyses below based on these low but not insignificant rates. Finally, to ensure that our final timepoint which has a longer time gap does not overly influence the findings, we will examine transformations of the time axis.

**AIM 2:** Determine whether intervention effects are partially mediated by family communication and externalizing behaviors, including drug misuse, and moderated by parental depression.

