**Power Analyses:** For continuous effectiveness outcomes, such as the slope of depressive symptoms over the 18 months, we have 87% power to detect an effect size of 0.5 (Type I error 0.05), which is the median effect size we found in a previous synthesis project investigating reduced depressive symptoms in 19 prevention programs with a two year follow-up (see Figure 5 in the following reference). We expect this effect size given that we are now including youth who are elevated on depressive or anxiety symptoms or have a history of suicide ideation or attempts. For suicide ideation, our growth models for repeated binary measures indicates we will have over 70% power to detect a yearly odds ratio (OR) reduction of 0.50 when the prevalence of ideation at baseline is 0.12 (or 12%). For suicide attempts, the baseline prevalence we have observed previously is 0.086 (or 8.6%), and this provides 55% power to detect an OR of 0.5. These ORs and prevalence rates were taken from our most recent Familias Unidas trials using the subset of youth with poor family communication, matching our inclusion criteria. For suicide attempts, if we obtain an OR of 0.4, we would have 71% power to detect this change from baseline for attempts and 88% power for ideation. We will analyze impact on K-CAT MDD as well as use missing data and a two-stage design to calibrate these findings against K-SADS MDD, see section 4.4.). Thus, we have sufficient power to detect a large effect on suicide outcomes over time. For the power of detecting a mediation effect, we take as an example 6-month family communication mediating 18-month depressive symptoms. If both the a and b estimators have 80% power of rejecting their nulls, then the product has a 64% power of rejecting the mediation pathway as being significant. If each a and b estimators have 85% power, the product has 72% power of rejection. Additional details are provided in Clinical Trials Section 4B.

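### The suicide power figures rest on baseline rates other than those the Aim 1 text cites, and the sufficiency claim that follows them does not hold for suicide attempts

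*Protocol*

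**What the plan says.** In protocol section 7, the Aim 1 analysis text gives baseline rates from a universal trial, 9.2% for ideation and 5.7% for attempts, and continues: "We have presented power analyses below based on these low but not insignificant rates".

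The Power Analyses paragraph of the same section uses different rates:
- Ideation at 12%: over 70% power for a yearly OR of 0.50, and 88% for an OR of 0.4.
- Attempts at 8.6%: "and this provides 55% power to detect an OR of 0.5", and 71% for an OR of 0.4.

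It says that the ORs and rates come from earlier trials, "using the subset of youth with poor family communication, matching our inclusion criteria", and concludes: "Thus, we have sufficient power to detect a large effect on suicide outcomes over time".

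Two other places bear on this. The crossover-effects text under Preliminary studies (section 3) reports 12.2% ideation and 8.6% attempts in youth with poor family communication, and says that in them the intervention "significantly reduced suicide attempts compared to control (OR = .53". Criterion (e) in section 4 admits families with poor communication, or "youth reporting elevated depressive or anxiety symptom scores or a history of suicide behavior (ideation or attempts".

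**The concern.** H1 in section 2 names suicide ideation and behavior among the effectiveness outcomes, so the stated power tells the reader how to take a null result. Four things do not fit together:

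1. One paragraph says that power was computed at 9.2% and 5.7%; the next computes it at 12% and 8.6%.
2. The subset is said to match eligibility, but eligibility is an either/or rule with further routes of entry. The Power Analyses paragraph itself relies on those routes to justify the depression effect size.
3. The ORs are attributed to earlier trials, yet the document reports only one suicide OR: .53, for attempts, with no time scale. No ideation OR and no OR of 0.4 is reported.
4. One sentence declares sufficient power for suicide outcomes together, although attempts have 55% and 71%.

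A reader who relies on that sentence could take a null attempts result as evidence of no effect, when the trial has only about even odds of detecting the effect seen before.

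**Working it through.** **Inputs from the protocol.** Section 5: "The sample will consist of 468 Hispanic female and male adolescents and their primary caregivers recruited from one of 18 primary care clinics", and "Youth and parents will be assessed at baseline, 3-, 6-, and 18-months post-baseline". Type I error is 0.05. Rates, ORs and power are as listed above.

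**Assumptions, because the protocol does not give them.** 234 youth per condition; two-sided test; flat control trajectory; the attempts OR is yearly, as stated for ideation; retention 100/95/92/85% over the four visits; exchangeable visit correlation 0.25. There is no explicit clinic or calendar term.

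**Reproducing the stated figures.** The test is a Wald test of the slope difference on the logit scale, with visits at 0, 0.25, 0.5 and 1.5 years:

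λ = |ln OR| / SE, power = Φ(λ − 1.96), with SE from the GEE information matrix.

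| Outcome, rate, yearly OR | λ | Power | Stated |
|---|---|---|---|
| Ideation 12%, 0.5 | 2.469 | 70% | over 70% |
| Attempts 8.6%, 0.5 | 2.104 | 56% | 55% |
| Attempts 8.6%, 0.4 | 2.546 | 72% | 71% |
| Ideation 12%, 0.4 | 2.999 | 85% | 88% |

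The stated figures are plausible for their own inputs, so no arithmetic error is shown. The match is not unique: other correlations without dropout also come close to individual figures.

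**Restating power.** To depend little on the assumed correlation and dropout, I scale the protocol's own power. The stated non-centrality is 1.96 + z(power):
- Ideation: 1.96 + 0.524 = 2.484, taking over 70% as 70%.
- Attempts: 1.96 + 0.126 = 2.086.

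Each is multiplied by the ratio of new to old λ:

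- Ideation at 9.2%, OR 0.5: ratio 2.174/2.469 = 0.881. 2.484 × 0.881 = 2.188; Φ(0.228) = **59%**.
- Attempts at 5.7%, OR 0.5: ratio 1.721/2.104 = 0.818. 2.086 × 0.818 = 1.706; Φ(−0.254) = **40%**.
- Attempts at 8.6%, yearly OR 0.53: ratio 1.969/2.104 = 0.936. 2.086 × 0.936 = 1.952; Φ(−0.008) = **50%**.

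These move by less than 2 points for visit correlations from 0 to 0.6. A design allowance that multiplies every variance by one factor cancels in the ratio.

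**Hand check.** If the variance goes as 1/[p(1−p)], the ratio is √(0.092 × 0.908 / (0.12 × 0.88)) = 0.889 for ideation and √(0.057 × 0.943 / (0.086 × 0.914)) = 0.827 for attempts. These give about 60% and 41%.

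**Direct calculation without scaling or dropout.**
- Attempts at 5.7%, OR 0.5: 40% (37–48% for correlations 0 to 0.3).
- Ideation at 9.2%, OR 0.5: 62% (53–67%).
- Attempts at 8.6%, OR 0.53: 49% (45–59%).

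**The other direction.** Criterion (e) may enrol youth at higher risk than the subset. With illustrative prevalences and yearly OR 0.5:
- Ideation at 20%: 2.484 × 1.269 = 3.152, so 88%.
- Attempts at 12%: 2.086 × 1.173 = 2.447, so 69%.

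**The case against.** The 12% and 8.6% are not stray numbers. They agree with the subset rates in section 3, and the power paragraph names that subset. The conflict is with one sentence in the Aim 1 text, and the universal rates are not obviously the right ones for a trial that selects on risk. This stands: 59% and 40% show what the Aim 1 sentence implies, not what the trial will have. Wider eligibility could raise power.

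The step from 0.53 to 0.50 is close to rounding and costs about 5 points. This also stands. The power paragraph refers to trials in the plural, so an unreported OR may exist; the document does not show it.

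The sufficiency sentence is limited to a large effect and follows the OR 0.4 results, including 88% for ideation. The 55% is disclosed and is not itself called sufficient. That is fair for ideation, but attempts reach only 71% even at that larger OR.

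Stronger readings that a reader might infer are not supported:
- That .53 is a cumulative OR over the whole follow-up, so that power is far lower. The document gives no time scale.
- That the figures ignore the rollout design. The reproduction is consistent with this but does not show it, and further details are referred to a Clinical Trials section that is not part of this document.
- That the trial would usually miss the earlier attempts effect. About 50% is even odds.
- That attempts must leave H1 testing. Low power does not invalidate a test.

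**Conclusion.** The point holds as an inconsistency of inputs and an over-broad conclusion. The Aim 1 text misstates the rates behind the power figures; at the rates it cites, power is about 59% for ideation and 40% for attempts. The claim that the subset matches the inclusion criteria is inaccurate, with an error that may well be conservative. For attempts, power is about 50–55% at roughly the only documented OR and 71% at an OR of 0.4 that is reported nowhere. Of the four stated figures, only ideation at OR 0.4 exceeds 80%. The sufficiency sentence is therefore unsupported for attempts.

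The restated figures assume an equal split, a two-sided test, yearly ORs and a slope test of the kind described. The contradiction between the two paragraphs and the 55% and 71% figures need no assumption.

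**What to change.** 1. Correct the Aim 1 text so that one set of baseline rates underlies the power analyses, and say which population it comes from.
2. Delete the claim that the subset matches the inclusion criteria, or give power over a prevalence range suited to criterion (e).
3. State the time scale of the OR, and report attempts power at .53 alongside 0.5 and 0.4.
4. Replace the sufficiency sentence with separate statements for ideation and attempts. For attempts, say that power is only about 50–55% at the previously observed OR (at 8.6% prevalence, read as yearly), so a null result there would be inconclusive.

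The cost is a short power rerun and a few sentences. The claim for attempts becomes less favourable; enrolment and the planned analyses do not change.

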#### Risks to Subjects\*

We do not expect that there will be any negative consequences from participating in this study. However, the sensitive nature of some intervention topics (e.g. sexual behaviors and drug use) may be embarrassing and/or distressing to some participants. It is also possible that they may feel tired after answering the questionnaires, or made uncomfortable by the questions.

If a parent or adolescent reports elevated levels of depression, or if an adolescent reports incidence of suicidality, he or she will be directed to speak with a facilitator for further assessment. If necessary, a referral will be made for additional services.

Video session recordings will be saved onto secure university servers. All data with identifiable information such as names, date of birth, etc., will be numerically labeled and kept separate from assessment data. Only PIs and authorized study personnel will have access to data files and participant linking lists. The risks associated with gathering information from participants by properly trained and supervised professional research staff are low and include risks of loss of privacy and transient psychological distress. The research team has extensive experience in conducting intervention and assessment protocols that involve underserved populations as well as highly confidential personal information. Quality assurance protocols, emergency procedures, and crisis intervention, and referral procedures have been established in previous trials and can be modified as needed for the proposed study.

We will conduct data analysis of deidentified clinical notes that are taken as part of our existing procedures to triage adolescents who have reported incidence of suicidality on the assessment battery. This is data that has resulted from existing study procedures; there are no new study procedures being added. When adolescents have reported incidence of suicidality and they have been triaged by a study team member, documentation of these incidents will be the source of data. We will analyze the data to extract common themes that may emerge in a summary format without identifiable participant characteristics and/or information.

## **8) Potential Benefits to Subjects\***

There may be direct benefits to participating in this study. Adolescents may be less likely to use drugs and engage in risky behaviors such as having sex without a condom. Also, adolescents may have decreases in depression and anxiety symptoms and suicide thoughts or acts. Additionally, families may communicate more effectively. This study also has the potential to provide knowledge regarding how to best implement evidence-based interventions in primary care settings where it can be offered to Hispanic youth, a population with historically low access to preventive interventions.

## **9) Vulnerable Populations\***

The research involves children under the age of 18. To avoid coercion or undue influence, the adolescents will assent and complete assessments separate from their primary care giver. In case the adolescent does not want to assent, the family will be told they did not meet one or more of the inclusion/exclusion criteria but the facilitator will not reveal to the parent that the child did not assent (to avoid any consequences to the child).

[name] has a long track record of working with [name] which extends over 10 years. For this study, [name] will collaborate with the senior investigative team in the adaptation of eHealth Familias Unidas along with planning the outcome analyses and preparing manuscripts for publication. [name] will also be responsible for coordinating the research and research-clinical interface aspects of the study.

[name], Clinical Trainer and Supervisor is a Licensed Clinical Social Worker with over 20 years of experience working with Hispanic families. She is trained in delivering family-based interventions, including eHealth Familias Unidas, to Hispanic parents and their youth. [name] has engaged over 80% of Hispanic parents into the Familias Unidas intervention over the past 15 years. She also has extensive experience training and supervising the Familias Unidas model. For the proposed study, [name] will be responsible for training and supervising the primary care facilitators in the delivery of the intervention. She will also conduct the supervision meetings with the primary care facilitators and will help them problem solve potential barriers of intervention engagement and retention. Additionally, [name] will handle any adverse or serious adverse events that may occur during the intervention sessions. [name] will also provide input regarding development of the new intervention modules in year 1.

Assessors will be responsible for screening potential study participants and conducting the parent and youth assessments over the four years. Assessors will conduct over 7,000 assessments over the four years (i.e., 468 youth and 468 parent assessments per assessment timepoint x 4 assessment timepoints). They will also be responsible for scheduling these assessments. Finally, assessors will also be responsible for maintaining cordial contact in between assessment timepoints, in order to maximize retention rates at assessments.

Other study personnel, such as student, research assistants and facilitators will be trained in study

## **12) Prior Approvals**

None.

## **13) Recruitment Methods**

Screening will take place in pediatric care clinics. Screening will be included into the patient check-in process. Parents and adolescents will complete the screening separately on tablets provided by the research team. REDCap programming will be used to determine whether the participant meets the screening criteria. Families who meet study inclusion/exclusion criteria will automatically be connected via protected videoconference software to the on-call study team via iPad to complete the e-consent process. If a videoconference call is not possible, arrangements will be made at a convenient time for the participant. The team member will explain the study to eligible participants and complete the e-consent process. Families who enroll will then be sent a link to complete the assessment battery via iPad while they wait for the physician. The clinic staff member will thank the study participant for enrolling in the study and will make a hand off to the physician. We will screen and enroll youth with poor family communication or elevated depressive or anxious symptoms, as well as those with a history of

suicide ideation or attempts (see inclusion criteria).

Participants will be assessed at baseline and 3-, 6-, and 18- months post-baseline. We have budgeted the following amounts for participant parent incentives: T1=\$40, T2=\$45, T3 = \$50 and T4= \$55. Adolescents will receive two movie tickets and \$20 for each completed assessment. The participant incentive cost will reimburse study participants for time and effort to participate in the baseline and each of the follow-up assessment activities.

As an additional form of recruitment, clinic doctors will also provide families with a note where they recommend the program. If the family is interested in participating, they will provide their contact information and a research team member will call them to explain the study. We will also distribute flyers in the clinics to recruit participants. These flyers will contain a QR code that can be scanned by potentially interested participants. Once scanned, participants will be able to provide their contact information so that they can be reached and given more information about the study.

Additionally, we will do the following:

Research study staff will request permission from each clinic, at UM clinics only and not at any external clinics, to have access to their scheduling system. On a daily basis, research study personnel will access data on which individuals have a scheduled appointment. No health information will be available to research study staff, only parent name, child age and whether there is an appointment scheduled. Study staff will use the study's screening form to screen these individuals, at the clinic, to see which meet criteria. Study staff will then go to waiting room to recruit those that meet criteria.

**Registry Recruitment** –We will also collaborate with the University of Miami's Clinical & Translational Science Institute (CTSI) Consent to Contact registry to identify potential participants. They will provide us with contact information for patients who have provided permission to be contacted by study projects. We will send out a general recruitment flyer, email, or text (depending on a participant's preferred choice of contact) to these families and we will invite them to complete the REDCap screening survey and consent if they are interested in the eHealth Familias Unidas for Mental Health project. A partial waiver of HIPAA is requested to utilize the Consent to Contact database

